General information	√				
Numbness VAS score	√	√	√	√	√
Nylon rope test	√	√	√		
Needle punching test	√	√	√		
JOA score	√	√	√	√	√
Lower Limb EMG	√	√	√		
Chinese medicine evidence score	√	√	√	√	√
SF-36 (Quality of Life Scale)	√	√	√	√	√
VAS score	√	√	√	√	√
Safety observations		√	√	√	√

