### Statistical analysis

2.12

Sample size calculation was performed using PASS software (version 15.0, NCSS LLC). Based on preliminary data, the estimated mean (standard deviation) of the VAS numbness score after intervention for the treatment group (UA + WA) is 1.6 ± 1.0 cm, and for the control group (electroacupuncture) it is 2.41 ± 1.68 cm. To detect a between-group difference of 0.81 cm with 90% power (*β* = 0.10) and a two-sided *α* of 0.05, at least 41 participants are required in each group. Considering a 15% dropout rate, the final sample size is set at 48 participants per group (96 participants in total). This calculation complies with the CONSORT guidelines for randomized controlled trials.

All analyses will follow the intention-to-treat (ITT) principle, including all randomized participants. Additionally, for sensitivity analysis, a per-protocol set (PPS) analysis will be conducted, excluding participants with major protocol deviations (e.g., fewer than 8 acupuncture sessions, and use of prohibited medications). The primary outcome, the change in VAS numbness score over time points (baseline, 1 week, 4 weeks, 12 weeks, 24 weeks), will be assessed using a linear mixed-effects model (LMM). The model will include group, time, group-by-time interaction, and baseline VAS score as fixed effects. Random intercepts and slopes will account for within-individual variability. Missing data will be handled using multiple imputation (MI) with fully conditional specification (FCS) in SAS 9.4 (SAS Institute), generating 10 imputed datasets. Estimates will be combined according to Rubin’s rules. Sensitivity analysis will compare MI with the last observation carried forward (LOCF). For secondary outcomes with continuous variables (e.g., JOA, SF-36), the same LMM structure as the primary outcome will be used. For ordinal/categorical variables (e.g., TCM syndrome score), proportional odds logistic regression or generalized estimating equations (GEE) will be applied to longitudinal ordinal data. For binary outcomes (e.g., adverse events), comparisons between groups will be made using the chi-square test or Fisher’s exact test (for small sample sizes). Risk ratios (RR) and 95% confidence intervals (CI) will be reported.

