The success of assessor blinding will be evaluated using James’ blinding index. A value close to 0.5 indicates effective blinding (0 = completely unblinded; 1 = completely blinded). If there are baseline differences (e.g., age, baseline VAS score), adjustments will be made using analysis of covariance (ANCOVA). Pre-specified subgroups (e.g., age < 50 vs. ≥ 50 years, baseline VAS score severity) will be explored using interaction terms in regression models. *p*-values will be adjusted using the false discovery rate (FDR) correction for multiple comparisons for the primary outcome.

Adverse events (AE) will be graded according to CTCAE v5.0. The incidence rates between groups will be compared using the chi-square test (or Fisher’s exact test for rare events). Descriptive analysis will be conducted for serious adverse events (≥ grade 3). Analyses will be performed using SAS 9.4 (SAS Institute) and SPSS 26.0 (IBM Corp). Continuous outcomes will be reported as mean differences (MD) with 95% CI and effect sizes (Cohen’s d). Categorical outcomes will be reported as risk ratios (RR) with 95% CI. Exact *p*-values will be provided for all tests, with a significance level set at *p* < 0.05 for the primary outcome.

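### Ordinary proportional odds regression is allowed as an alternative to GEE for repeated ordinal outcomes, with no provision for within-patient correlation

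*Protocol article*

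**What the plan says.** In section 2.12 (Statistical analysis) the rule for these outcomes opens "For ordinal/categorical variables (e.g., TCM syndrome score" and continues that "proportional odds logistic regression or generalized estimating equations (GEE) will be applied to longitudinal ordinal data". Both methods are attached to longitudinal data. No rule for choosing between them is given, and no patient effect or clustered standard error is attached to the first.

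Table 1 in section 2.8.2 lists the TCM score as "Chinese medicine evidence score" and schedules it at baseline, at 1 and 4 weeks, and at 12 and 24 weeks after treatment. The monofilament test, scored 3, 2 or 1 in section 2.8.2, is scheduled at baseline, 1 week and 4 weeks.

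For the primary numbness VAS the same paragraph of section 2.12 does deal with repeated measurement: "Random intercepts and slopes will account for within-individual variability". It carries that structure over to the continuous secondary outcomes, but not to the ordinal ones.

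**The concern.** Patients are randomised, and each contributes several visits. Scores from one patient are correlated, so four visits carry less information about a difference between arms than four patients would. A cumulative-logit model fitted by ordinary maximum likelihood to one row per visit counts each row as a separate patient. The standard error of an average group effect is then too small. The standard error of a change in the group effect between visits is too large.

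The two named methods are therefore not interchangeable for repeated data, and they can give materially different p-values from the same records. At stake is whether a null TCM or monofilament result is reported as a difference too often, or a real change over visits is missed. Section 2.12 promises exact p-values for all tests but ties both the FDR correction and the 0.05 level to the primary outcome, so nothing else in the text would temper an anti-conservative secondary p-value.

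**Working it through.** The article gives no error rate, within-patient correlation or category frequencies for the ordinal outcomes, so there is no figure of its own to reproduce. The check asks what happens if the first named option is fitted to stacked visits.

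**Inputs from the article**
- Visits after baseline (Table 1): m = 4 for the TCM score, m = 2 for the monofilament score.
- Level: two-sided 5%. The article fixes it for the primary outcome; here it is assumed for the secondary outcomes.
- Patients: 41 per arm, from "at least 41 participants are required in each group". That is the minimum for the VAS and is assumed here to be the evaluable number.

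**Assumed inputs**
- Equal correlation rho between all visits of a patient: 0.3, 0.5 or 0.7.
- Equally likely categories: four for the TCM score, three for the monofilament score.
- No true difference between arms.

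**1. Pooled group effect, by formula.** Ignoring the correlation understates the variance by DE = 1 + (m - 1) × rho. The actual error is 2 × [1 - Φ(1.96/√DE)].
- m = 4: rho 0.3 gives DE 1.9 and 15.5%; rho 0.5 gives DE 2.5 and 21.5%; rho 0.7 gives DE 3.1 and 26.6%.
- m = 2: DE is 1.3, 1.5 and 1.7, giving 8.6%, 11.0% and 13.3%.
- With adjustment for the baseline score, the residual correlation is rho/(1 + rho). For m = 4 the errors become 13.2%, 16.6% and 19.0%.

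**2. Group-by-visit contrast, by formula.** The true variance is (1 - rho) times the assumed one, so the error is 2 × [1 - Φ(1.96/√(1 - rho))]: 1.9%, 0.6% and 0.03%.

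**3. Simulation under the null.** A latent normal score was cut into categories and an ordinary proportional odds model was fitted to stacked visits. Rejection rates at nominal 5%:

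| Test | rho 0.3 | rho 0.5 | rho 0.7 |
|---|---|---|---|
| TCM, pooled group effect, no baseline term (41 per arm, 600 trials) | 13.7% | 17.3% | 25.8% |
| The same, with baseline term | 11.8% | 14.8% | 19.5% |
| TCM, pooled group effect, no baseline term (48 per arm, 1,500 trials) | 14.9% | 20.2% | 26.5% |
| The same, with baseline term | 11.7% | 16.7% | 20.2% |
| TCM, model with group-by-visit: group coefficient at the reference visit (41 per arm, 800 trials) | 5.9% | 5.6% | 5.0% |
| TCM, same model: joint group-by-visit test | 2.5% | 0.8% | 0.0% |
| Monofilament, pooled group effect, no baseline term (41 per arm, 600 trials) | 8.0% | 9.3% | 11.5% |
| The same, with baseline term | 8.0% | 8.0% | 8.7% |

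A further run at 41 per arm over the same correlations gave 11-24% for the pooled TCM group effect, 12-23% for the visit-averaged effect when group-by-visit terms are in the model, and 0-2% for the joint interaction test.

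The runs agree within simulation error. At rho 0.5 without baseline, 17.3% has standard error √(0.173 × 0.827/600) = 1.5 points and 20.2% has √(0.202 × 0.798/1500) = 1.0 point. The formula lies somewhat higher because cutting the score into categories lowers the observed correlation below rho.

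**4. Does the remedy work?** With patient-clustered standard errors the pooled TCM group test rejects about 4-6% at 41 per arm and 4.3-6.6% at 48 per arm. Proportional odds regression at a single visit rejects 4.8%.

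**The case against.** The strongest reply is that the article never describes the faulty analysis. It does not say that visits are stacked, that the patient is ignored, or which coefficient is tested. The sentence can be read as proportional odds for one visit and GEE across visits, and on that reading nothing is wrong. Proportional odds is a model and GEE a way of estimating, so the two can also be combined. The random effects for the continuous outcomes show that the authors know of the correlation, and a SAP that is not shown may settle the choice. This stands as a reason to treat the error rates as conditional. It does not clear the sentence, which assigns both methods to longitudinal data without saying when each applies.

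A second reply is that the only longitudinal model the article spells out has a group-by-time term, and that with such a term the inflation disappears. This holds for the group coefficient at one visit (5.0-5.9%). It does not hold for the group effect averaged over visits, which still rejects 12-23%, and the joint interaction test errs the other way.

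Third, the stakes are modest. The outcomes are secondary, and the article commits to a significance level only in the words "with a significance level set at *p* < 0.05 for the primary outcome". Section 2.4 keeps the statisticians unaware of allocation. That limits steering the choice towards one arm, although it does not hide which method gives the smaller p-value.

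A reader might go further and infer that the plan sets the TCM false-positive rate at 15-17%. The article does not support that. The figure needs stacked visits, a pooled effect, a particular correlation and assumed categories, none of which it states.

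**Conclusion.** The point holds in a conditional form. Section 2.12 permits, for repeated ordinal outcomes, a method that as named makes no allowance for within-patient correlation, and gives no rule that confines it to single visits. If it were fitted to stacked visits with 41 per arm, equal categories and correlations of 0.3 to 0.7, then:
- the pooled or visit-averaged group effect on the TCM score would be falsely significant in roughly 11-26% of null trials instead of 5%;
- the pooled group effect on the monofilament score would be so in about 8-12%;
- the joint group-by-visit test on the TCM score would reject only about 0-3%, which costs power.

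Weaker or stronger correlation widens the range: for the pooled TCM effect without baseline adjustment the formula gives 8.6% at 0.1 and 28.8% at 0.8. Single-visit comparisons keep their level. Only secondary outcomes are concerned; the numbness VAS model has patient-level random effects and is untouched. The wording should be corrected, but it does not threaten the trial's main conclusion.

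**What to change.** Replace the ordinal sentence in section 2.12 with, for example: *Repeated ordinal outcomes will be analysed with a cumulative-logit GEE, with the patient as cluster and robust standard errors, and with group, visit, group-by-visit and baseline score as terms. Ordinary proportional odds regression will be used only for analyses of a single visit.*

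A cumulative-logit mixed model with a patient random intercept would serve equally well. One of the two should be named, because leaving both would reopen the choice.

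The cost is one sentence, settled before the data are analysed. No new data are needed, and SAS 9.4, already named, can fit either model. The downside is wider, correct confidence intervals for the averaged group effect. With four visits and a correlation of 0.5 they would be about √2.5 = 1.6 times as wide as the uncorrected ones, or √2.0 = 1.4 times after baseline adjustment (DE = 1 + 3 × 0.333). Intervals for group-by-visit contrasts would become narrower, by about √0.5 = 0.7.

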#### Secondary outcome

2.8.2

Nylon Filament Test (10 g Monofilament Test): A 10 g monofilament is used to stroke the skin area where the patient feels numb. The numb skin area is stroked 10 times, and the number of strokes perceived is observed and recorded. Perceiving 7–10 strokes is considered normal, 1–6 strokes is considered reduced sensation, and 0 strokes is considered absent sensation. The researcher records these as 3 points, 2 points, and 1 point, respectively. The study indicates that tactile static testing using a 10 g monofilament demonstrates the highest sensitivity for detecting superficial sensory disturbances. It can be recommended as the most sensitive single testing tool (28).

Pinprick Test (40 g Pressure Pinprick Test): A blunt-tipped pressure needle is used to apply a constant force to the patient’s numb area. The presence or absence of pain is observed and recorded, with pain scored as 1 point and no pain scored as 0 points. The experiment differentiates neuropathic pain from sensory loss by assessing Aδ fiber function, with sensitivity and specificity ranging from 68 to 85% and 79 to 92%, respectively (29). The test demonstrates good reproducibility (ICC = 0.89) in the assessment of postoperative neuropathy (30).

Other secondary indicators: JOA (Japanese Orthopedic Association) Score, a study mentioned that the JOA scoring system was used to evaluate 89 patients who underwent lumbar decompression surgery, and it was found that 30.3% of patients still had mild lower extremity pain/numbness and 14.6% of patients still had gait disturbances 2 years after the surgery. This indicates that the JOA scoring system can effectively identify residual symptoms after surgery (31). Traditional Chinese Medicine Syndrome Score, the TCM Syndrome Score does not focus solely on individual symptoms, but rather considers multiple symptoms and signs comprehensively, providing a more holistic assessment of the patient’s condition, it has high effectiveness in evaluating treatment outcomes (32). Additionally, Lower Limb Electromyography (H-reflex difference, F-wave conduction velocity, and latency), VAS Score, SF-36 (Short Form 36 Health Survey Questionnaire). The evaluation time points are detailed in Table 1.

**Table 1 tab1:** Timeline for the collection of evaluation indicators.

Observation indicators	Pretreatment	Treatment stage		Follow-up phase	
	Baseline (in geodetic survey)	1 week	4 weeks	12 weeks after treatment	24 weeks after treatment

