### Data collection and management

2.10

After participants sign the informed consent form, researchers will collect personal information such as general demographic information, clinical history, as well as baseline data including the Numbness VAS Score, 10 g Monofilament Test, 40 g Pressure Pinprick Test, JOA Score, Lower Limb Electromyography (H-reflex difference, F-wave conduction velocity, and latency), VAS Score, Traditional Chinese Medicine Syndrome Score, SF-36 (Short Form 36 Health Survey Questionnaire), etc. Outcome measures will be assessed at specified time points and recorded in the CRF. After the trial, two researchers who are not involved in data distribution or outcome assessment will independently extract data from the CRF into an Excel table. A statistician will then perform statistical analysis on this data after careful review and confirmation. To protect participant privacy, personal names will be replaced with a combination of numbers and initials. Researchers shall keep the data confidential for 5 years after the trial termination. To reduce participant dropout rates, researchers will call participants 2 days before treatment to inquire about their condition and encourage them to receive treatment as scheduled.

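### By its wording, the rule for binary outcomes gives the repeated 0/1 pinprick test an unadjusted chi-square or Fisher test, leaving its baseline value unused

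*Protocol article*

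**What the plan says.** Section 2.8.2 defines the pinprick result as binary, "with pain scored as 1 point and no pain scored as 0 points". Section 2.10 includes it among the baseline data ("40 g Pressure Pinprick Test, JOA Score, Lower Limb Electromyography"). Table 1, in the row labelled "Needle punching test", schedules it at baseline, 1 week and 4 weeks, and not at 12 or 24 weeks.

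Section 2.12 then assigns methods by type of outcome:

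- **Continuous secondary outcomes** take the structure of the primary model: "The model will include group, time, group-by-time interaction, and baseline VAS score as fixed effects", with random effects for repeated measures.
- **Ordinal/categorical outcomes**, with the TCM syndrome score as the example, get proportional odds regression, or "generalized estimating equations (GEE) will be applied to longitudinal ordinal data".
- **Binary outcomes**: "For binary outcomes (e.g., adverse events), comparisons between groups will be made using the chi-square test", or Fisher's exact test for small samples. Risk ratios with 95% CI are reported.

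Later in the same section there is a conditional provision: "If there are baseline differences (e.g., age, baseline VAS score), adjustments will be made using analysis of covariance (ANCOVA". Adverse events also get their own chi-square/Fisher sentence there.

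**The concern.** The pinprick test is the only efficacy outcome in section 2.8 that the article defines as 0/1. It has the same repeated design as the monofilament test and the electromyography. Yet the method for its type of outcome has no term for baseline and none for visit. Followed as written, it would be compared by a separate two-by-two table at each visit, with the baseline result set aside.

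If sensation at baseline predicts sensation at 4 weeks, that discards information already paid for and leaves chance baseline imbalance in the comparison. At stake is precision on a secondary outcome that does not rest on the numbness VAS, which the Discussion itself lists as a subjective measure. The primary analysis is not affected.

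**Working it through.** **Step 1. Which rule covers pinprick?** The binary sentence offers adverse events as an example, not as a limit. Adverse events have their own sentence further on, so a general binary rule adds something only if it reaches another binary outcome, and pinprick is the one defined. The GEE clause is worded for ordinal data, and binary outcomes have a separate sentence after it. On the wording, pinprick falls under chi-square/Fisher.

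**Step 2. Does the ANCOVA clause repair this?** No. It applies only once an imbalance has been seen, it is a method for continuous outcomes, and it does not model the repeat visits.

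**Step 3. Inputs for size.** The article has no sample-size figure for pinprick, so there is none to reproduce. The evaluable number is taken from section 2.12: 41 per group (48 × 0.85 = 40.8). Whether 41 is right for the primary outcome is a separate matter. Everything else is assumed: week-4 rates of 50% and 75%, baseline prevalence of 10%, 30% or 50%, and a latent correlation between visits from 0 to 0.85.

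**Step 4. Chi-square power by formula.** The mean rate is (0.50 + 0.75)/2 = 0.625.

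- Null SE = √(2 × 0.625 × 0.375 / 41) = 0.1069
- Alternative SE = √((0.50 × 0.50 + 0.75 × 0.25) / 41) = 0.1033
- Power = Φ((0.25 − 1.96 × 0.1069) / 0.1033) = Φ(0.39) ≈ 0.65

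**Step 5. Simulation of the week-4 comparison.** There were 10,000 trials per cell, with latent-normal binary data and exchangeable correlation. Each cell gives the power of the uncorrected chi-square test → the power of a Mantel-Haenszel test stratified by baseline pinprick (the score-test analogue of logistic regression with that covariate), with the change in points.

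| Latent correlation | Baseline 10% | Baseline 30% | Baseline 50% |
|---|---|---|---|
| 0 | 0.666 → 0.656 (−1.0) | 0.661 → 0.651 (−1.0) | 0.675 → 0.662 (−1.3) |
| 0.3 | 0.660 → 0.654 (−0.6) | 0.666 → 0.667 (+0.1) | 0.667 → 0.670 (+0.3) |
| 0.5 | 0.665 → 0.670 (+0.5) | 0.670 → 0.690 (+2.0) | 0.672 → 0.699 (+2.7) |
| 0.7 | 0.662 → 0.675 (+1.3) | 0.669 → 0.735 (+6.6) | 0.663 → 0.759 (+9.6) |
| 0.85 | 0.664 → 0.688 (+2.4) | 0.667 → 0.763 (+9.6) | 0.660 → 0.832 (+17.2) |

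Simulation error is about half a point per power (√(0.66 × 0.34 / 10,000) = 0.0047). With no effect, rejection rates were 0.056 to 0.064 for chi-square and 0.047 to 0.054 for the adjusted test.

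**Step 6. Using both visits.** A baseline-adjusted analysis of the average of weeks 1 and 4, standing in for a GEE main effect, had power 0.78 to 0.93 if the effect is the same at both visits. If the week-1 effect is half as large (50% against 62.5%), power was 0.53 to 0.75, and so could fall below the 0.66 or so of the week-4 chi-square test. A smaller direct run of logistic regression and GEE (800 trials) was used only to check the pattern.

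**The case against.** **Pinprick is not named.** Section 2.12 nowhere mentions it, and the only example for the binary rule is adverse events, where chi-square/Fisher suits. The section also says categorical outcomes will be reported as risk ratios, so its use of categorical may include binary data, and the ordinal/categorical sentence with its GEE might be meant to cover pinprick. This stands in part: the assignment follows from the scale of the outcome, not from an explicit statement. The separate binary sentence and the restriction of GEE to ordinal data still make chi-square/Fisher the natural reading.

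**The detail may be in the analysis plan.** The Abstract refers to a predefined plan that is not shown, and covariates for one secondary outcome are often left to it. That would answer a complaint of silence. Here the article states a method for this type of outcome, and the point concerns what it states.

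**The plan does intend to adjust for imbalance.** It does, and the ANCOVA clause deserves mention, but it does not reach a repeated 0/1 outcome in usable form.

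**The gain is uncertain and the remedy can backfire.** Both stand. Entry requires a numbness VAS of at least 40 mm, not an abnormal pinprick result, so baseline pinprick could be mixed or almost constant. In the latter case adjustment gains little. Averaging the visits can lose power, so the target contrast has to be named.

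A reader might also infer that the chi-square analysis is biased or invalid, or that the trial is certain to lose power on this outcome. The documents support neither. Randomisation makes the comparison at a single visit valid, its error rate in the simulation was close to 5%, and the article contains nothing from which the correlation could be known.

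**Conclusion.** The point holds as one of efficiency and consistency. On its wording the article applies an unadjusted test to a binary efficacy outcome that has a baseline value and two later visits, while its continuous outcomes get baseline and time in the model.

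The likely cost lies between nothing and about 17 points of power at week 4. It is essentially nil at a latent correlation up to 0.3, about 1 to 10 points at 0.5 to 0.7, and about 2 to 17 points at 0.85, depending on baseline prevalence. These figures rest on 41 evaluable per group, assumed rates of 50% and 75%, and a stratified test standing in for the logistic model. The most that adjustment lost was 1.3 points, where baseline carried no information. The trial is not powered on pinprick, so this is a worthwhile improvement and not a threat to its main conclusion.

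**What to change.** In section 2.12, limit the chi-square/Fisher sentence to adverse events and add a sentence for pinprick. It would specify logistic regression at week 4, or a logistic GEE over weeks 1 and 4, with group, visit, group-by-visit and baseline pinprick. The week-4 group contrast, not the visit average, would be prespecified as the main comparison and reported as a standardised risk ratio with 95% CI. Standardising keeps the risk-ratio reporting already promised and avoids presenting a conditional odds ratio. An estimate with a standard error, taken on the log scale, also pools directly under the Rubin's rules step already planned.

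State a fallback for when baseline pinprick is nearly constant or cells are sparse, for example an unadjusted week-4 risk ratio with Fisher's exact test. Its trigger should be defined on counts pooled over the groups.

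The cost is a short text change made before outcome data are linked to allocation, plus a standardisation step and its variance in the programming. No extra visits, data or participants are needed.

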**Figure 2 fig2:**
[figure not shown]
Locations of acupoints.

After routine disinfection of CV 6, CV 4, the affected side’s ST 36, and GB 34, a 0.25 mm × 40 mm acupuncture needle is inserted directly, ensuring “Deqi” sensation is achieved at all acupoints. Once “Deqi” is reached, perform warm needle acupuncture at CV 6, ST 36, and GB 34; moxibustion uses moxa rolls with 1 cm lengths. During moxibustion, cardboard will be used as a shield to prevent burns.

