### Safety assessment

2.9

During the study, observations and records will be made of any potential adverse reactions, such as bleeding caused by acupuncture, hematoma, needle sickness, pain at the acupuncture site, infection, as well as skin rupture and infection after moxibustion. The primary records will include the incidence rate of adverse events and the grading of safety evaluations. Adverse events will be graded according to the Common Terminology Criteria for Adverse Events (CTCAE) Version 5.0. Mild (Grade 1): asymptomatic or mild symptoms, requiring no intervention; Moderate (Grade 2): symptoms are evident and require non-invasive treatment (such as local hemostasis, disinfection, etc.); Severe (Grade 3 and above): symptoms are severe, requiring hospitalization or leading to discontinuation of treatment. The evaluation time points are detailed in Table 1.

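### The risk ratio is the only effect measure stated for adverse events, but for moxibustion injuries its denominator is zero by design, and for other uncommon reactions it may be undefined

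*Protocol article*

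**What the plan says.** Section 2.12 (Statistical analysis) sends binary outcomes, with adverse events as the example, to a chi-square or Fisher test and adds: "Risk ratios (RR) and 95% confidence intervals (CI) will be reported". Later in the section the measure is repeated: "Categorical outcomes will be reported as risk ratios (RR) with 95% CI". On adverse events specifically it says "The incidence rates between groups will be compared using the chi-square test", with Fisher's exact test for rare events. Events of grade 3 or above are handled without a comparison: "Descriptive analysis will be conducted for serious adverse events (≥ grade 3").

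Section 2.9 (Safety assessment) lists the reactions to be recorded. Most are needling reactions that either arm can have, but the list ends "as well as skin rupture and infection after moxibustion". It then describes the main safety record: "The primary records will include the incidence rate of adverse events and the grading of safety evaluations".

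The arms differ in exposure. In section 2.6.1 (Intervention group) the acupuncturist is to "perform warm needle acupuncture at CV 6, ST 36, and GB 34", using moxa rolls. Section 2.6.2 (Control group) lists needling, electrical stimulation and an infrared lamp, and no moxibustion.

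**The concern.** A risk ratio divides by the control-arm incidence, so it has no value when that incidence is zero. For reactions to moxibustion the control incidence is zero by design. For other uncommon reactions, 48 participants per arm can easily leave the control arm empty by chance.

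The accompanying test does not fill the gap. Fisher's test stays valid with a zero cell, but it gives a p-value and no estimate. For a reaction that only one arm can have, it also tests a hypothesis already known to be false as soon as one event occurs.

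Safety is a stated objective, and the abstract's discussion anticipates a safer alternative to drug treatment. Burning moxa is a thermal hazard specific to the new regimen. There the reader needs an incidence with an interval, and the stated effect measure cannot supply a comparison.

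**Working it through.** **Inputs.** The protocol article gives 48 randomised per arm (96 in total), and 41 per arm after dropout (sections 2.5 and 2.12). It states no adverse-event rate and no precision target for safety, so there is no figure to reproduce. The rates r below are assumptions, taken as equal in both arms.

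**1. Moxibustion-specific reactions.** Let x be the number of treatment-arm participants affected. The control count is 0 because that arm is not exposed.

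Risk ratio = (x/48) / (0/48), which has a zero denominator for every x. This step needs no assumed rate.

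**2. Reactions that both arms can have.** The ratio is undefined when the control arm has no events.

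P(control arm empty) = (1 − r)^n

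| Assumed true rate r | n = 48 | n = 41 |
|---|---|---|
| 1% | 0.99^48 = 61.7% | 66.2% |
| 2% | 0.98^48 = 37.9% | 43.7% |
| 5% | 0.95^48 = 8.5% | 12.2% |
| 10% | 0.90^48 = 0.6% | 1.3% |

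A zero in the treatment arm alone gives a risk ratio of 0, which exists. Only the ordinary log-scale interval then fails. The chance that at least one arm is empty, 1 − (1 − q)² with q = (1 − r)^48, is 85.4%, 61.5%, 16.3% and 1.3% at the same rates. That is a different event and overstates how often the ratio itself is missing.

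**3. A reaction both arms can have, with 3/48 against 0/48.**

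- Risk ratio: 3/0, undefined.
- After adding 0.5 to each event count (and 0.5 to each arm total): (3.5/48.5)/(0.5/48.5) = 7.0. The log-scale SE is √(1/3.5 − 1/48.5 + 1/0.5 − 1/48.5) = 1.498, so the 95% CI is 7.0 × exp(±1.96 × 1.498) = 0.37 to 132.
- Fisher: p = 2 × C(48,3)/C(96,3) = 2 × 17,296/142,880 = 0.24.
- Risk difference: 6.25 points. The Wilson limits are 2.1% to 16.8% for 3/48 and 0% to 7.4% for 0/48. Newcombe lower limit: 6.25 − √((6.25 − 2.15)² + 7.41²) = −2.2. Upper limit: 6.25 + (16.84 − 6.25) = 16.8.

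The risk difference and its interval exist without any correction.

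**4. Five moxibustion injuries among 48 treated.**

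- Risk ratio: 5/0, undefined.
- Fisher: p = 2 × C(48,5)/C(96,5) = 2 × 1,712,304/61,124,064 = 0.056.
- Treatment-arm incidence: 5/48 = 10.4%, exact (Clopper-Pearson) 95% CI 3.5% to 22.7%.

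The test would be labelled non-significant at 5%, although an injury rate near 10% in the only exposed arm is the finding. If no injuries occurred, the exact interval would still exist: 0 to 1 − 0.025^(1/48) = 7.4%.

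**The case against.** The strongest reply is that the article never promises a risk ratio for each type of reaction. Section 2.9 puts overall incidence and grading first, and section 2.12 compares incidence rates between groups. That is naturally read as the proportion with any adverse event. With 15 scheduled sessions (3 + 3 × 4) and several minor needling reactions possible in both arms, that proportion may well not be rare, and its ratio would then exist. This stands, and it limits the point to reactions reported by type. It does not remove it: the types are listed, none is exempted from the risk-ratio rule, and one group can occur in one arm only.

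A second reply is that no interval method is named. A score interval for the ratio exists with one zero cell: for 3/48 against 0/48 it runs from 0.81 to infinity, and for 0/48 against 3/48 from 0 to 1.24. This also stands. A reader might infer that the plan leaves no interval at all for such events, and the document does not support that. For the moxibustion reactions, however, even a computable bound compares an exposed arm with an unexposed one and adds nothing to the incidence.

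A third reply is that a rule for zero cells usually belongs in the analysis plan, which is not shown. Its absence is therefore not the point. The point is the measure that the article does fix.

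A reader might also infer that the estimate will frequently be missing, that only a Fisher p-value would remain, or that a non-significant result will be presented as equal safety. The first depends wholly on assumed rates and fails at 5% and above. The second overlooks the recorded incidence and grading and the descriptive treatment of events of grade 3 or above. Nothing in the article states the third.

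**Conclusion.** The point holds in a narrow form. The only effect measure stated for adverse events cannot be formed for one listed group, the moxibustion reactions, and this rests on the article's own description of the two arms. For other reactions the ratio is undefined 62%, 38%, 9% or 0.6% of the time at true rates of 1%, 2%, 5% or 10% with 48 per arm. Those figures assume the rates and their equality between arms. The problem is therefore material at about 2% or below and minor from 5% up. The ratio for overall incidence would normally exist if events are not rare. No efficacy conclusion is affected. This is an inexpensive improvement to the safety reporting and not a flaw in the trial's main inference.

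**What to change.** Amend the adverse-event wording in section 2.12, and the analysis plan to match, before the data are analysed:

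- For every adverse-event comparison, report the number and percentage in each arm and the risk difference with a score-type 95% CI (Miettinen-Nurminen or Newcombe).
- Give a risk ratio with its 95% CI only where both arms have at least one event.
- For skin rupture and infection after moxibustion, report the treatment-arm incidence with an exact 95% CI, and make no between-arm test.

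This needs no new data and no change to conduct. The cost is a few lines of text and one more effect measure in the safety tables.
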